## Introduction

Multiple sclerosis (MS) is the most frequent cause of non-traumatic neurological disability in young adults in developed countries. Its prevalence has substantially increased in the last three decades and it affects ~2.3 million people worldwide (1, 2). The disease is associated with a high economic burden for society, and Spain is the European country with the highest total annual cost per patient (3, 4).

The clinical presentation of MS is heterogeneous and depends on the location of demyelinating lesions within the central nervous system. The most frequent symptoms and signs observed at disease onset originate from the optic nerve, the brainstem or cerebellum, the spinal cord, and the cerebral hemispheres (5). Motor manifestations (such as spasticity, gait, and balance impairments), optic neuritis, and sensory symptoms appear early in the disease course (6), and usually lead to progressive limitation of daily life activities. The majority of patients at the initial phase of MS have reversible episodes of neurological deficits (known as relapses) that usually last for days or weeks (relapsing-remitting MS; RRMS). Over time, in a proportion of patients, the development of permanent neurological deficits and the progression of clinical disability become prominent (secondary progressive MS; SPMS). A minority of patients have a progressive disease course from onset (primary progressive MS; PPMS). Most patients with MS, regardless of the initial disease course, will eventually require assistance to walk (7). It has been estimated that the average disease duration from diagnosis to use of a permanent walking aid is ~13 years (8). In fact, these motor problems have recently been identified by MS patients as the symptoms most undermining their health-related quality of life (HRQoL) (9).

Along with motor limitations, up to 65% of MS patients present impairments in a variety of cognitive domains within a year of diagnosis, processing speed being the most frequently affected domain in this time period (10). Deficits in memory, attention, executive functions, and visual perceptual functions are also prevalent in a considerable number of patients (11). The combination of all these impairments poses a threat to patients' daily life and is associated with work difficulties and negative outcomes (12, 13), including an early loss of productivity (14).

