The primary aim of this pilot study is to evaluate satisfaction with a VRR program in patients with MS at 6 months of program initiation.

Secondarily, we aim to: (i) describe adherence to a VRR and a CR program during 6 months; (ii) compare changes after 6 months of VRR or CR in a variety of domains typically affected by MS, including HRQoL, fatigue, activities of daily living (ADLs), work status, depression, anxiety, disability, spasms and spasticity, balance, and cognition; (iii) evaluate the presence of discomfort during the VRR program; (iv) explore clinical and demographic characteristics associated with patient satisfaction with the VRR program.

An exploratory data analysis of the secondary objectives described above will be performed at 1 month of rehabilitation program initiation.

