#### Demographic and Clinical Characteristics

Sociodemographic data (age, sex, educational level and profession) and clinical data (time from MS diagnosis, type of MS, use of DMTs, previous EDSS score, and clinical rehabilitation history) will be also collected.

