### Statistical Analysis Plan

To address the primary objective, the total score for USEQ in the VRR group with measures of central tendency and dispersion (mean, SD, median, minimum and maximum) will be presented.

To compare mean changes after 6 months of VRR or CR on domains typically affected by MS (HRQoL, fatigue, ADL, work status, depression, anxiety, disability, spasms and spasticity, balance, and cognition) an inferential analysis will be used. For variables that follow a normal (or parametric) distribution, a *t*-test will be used. For variables that do not follow a normal (or parametric) distribution, Mann-Whitney (for unpaired data) or Wilcoxon (for paired data) hypothesis tests will be used. For the analysis of the contingency tables and comparison of proportions and/or frequency distributions, the chi-squared test (or Fisher's exact test where appropriate) will be used. All tests will be 2-tailed, and *p* < 0.05 will be considered significant.

To investigate therapy adherence and discomfort during the VRR program, a descriptive statistical analysis will be performed. Measures of central tendency and dispersion (mean, SD, median, minimum and maximum) will be presented.

The association between clinical and demographic characteristics and patient satisfaction with the VRR program will be calculated using Pearson or Spearman correlation coefficients, as appropriate.

Absent data will not be accounted for and will be considered missing data. No imputation will be done. Parameter estimates and 95% confidence intervals will be reported for the principal quantitative outcomes. The Statistical Package for the Social Sciences (SPSS) software (v 22 or later) will be used to conduct the analysis. Further details of data analysis will be provided in a statistical analysis plan.

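### Objective (iv) names only Pearson or Spearman coefficients, which have no meaning for unordered characteristics with three or more categories, such as type of MS and profession (minor)

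*Protocol article*

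**What the plan says.** The aims at the end of the Introduction include, as the fourth secondary aim, to "explore clinical and demographic characteristics associated with patient satisfaction with the VRR program".

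The section Demographic and Clinical Characteristics gives the variables: "Sociodemographic data (age, sex, educational level and profession) and clinical data (time from MS diagnosis, type of MS, use of DMTs, previous EDSS score", followed by rehabilitation history.

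The Statistical Analysis Plan section covers the whole set in one sentence: "The association between clinical and demographic characteristics and patient satisfaction with the VRR program will be calculated using Pearson or Spearman correlation coefficients". The sentence ends with a qualifier, so that the association "will be calculated using Pearson or Spearman correlation coefficients, as appropriate". It names no other method for this aim. The section closes by deferring further analysis detail to a separate statistical analysis plan.

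The Introduction describes three disease courses: "relapsing-remitting MS; RRMS", "secondary progressive MS; SPMS" and a third: "A minority of patients have a progressive disease course from onset (primary progressive MS; PPMS". The Eligibility Criteria do not restrict the type of MS, so all three may be enrolled.

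**The concern.** Pearson and Spearman coefficients need values that are numeric or at least ordered. Profession has no order. Type of MS has none either: primary progressive disease is progressive from onset, so it is not a step beyond secondary progressive disease. DMT use and rehabilitation history would fall in the same class if they are recorded with several categories.

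The qualifier about appropriateness chooses between two coefficients, and neither suits these items. A coefficient for type of MS or profession would then reflect the order in which someone numbered the categories. It could change sign or vanish on renumbering, and it could hide a real difference between categories. That part of a listed secondary aim could not be interpreted.

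**Working it through.** **Which listed items the stated method fits**

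| Characteristic | Scale | Pearson or Spearman suitable? |
|---|---|---|
| Age, time from diagnosis, previous EDSS | numeric or ordered | yes |
| Educational level | ordered | yes (Spearman) |
| Sex | binary | yes; recoding changes only the sign |
| Type of MS | three unordered categories | no |
| Profession | unordered, several categories | no |
| DMT use, rehabilitation history | not stated | only if binary, ordered or numeric |

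**Whether another stated method covers the gap.** The t-test and Mann-Whitney sentences belong to the VRR versus CR comparison of mean changes, and they handle two groups at most. Chi-squared and Fisher tests are for contingency tables, whereas the USEQ total is a score from 6 to 30. Nothing named in the section compares a score across three or more groups.

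**Patients available.** The plan's VRR group size reproduces: (1.96 × 12 / 4.3)² = 29.9, so 30; 30 / 0.95 = 31.6, so 32. The associations would therefore rest on about 30 to 32 patients. The point does not depend on this figure.

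**Why the sign depends on the codes.** Assume 18 RRMS, 7 SPMS and 5 PPMS patients with mean USEQ 26, 22 and 26. These are illustrative inputs, not figures from the protocol. Only SPMS differs, by -4 points, so the covariance between code and group mean is

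-4 × (7/30) × (SPMS code − mean code).

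- Codes RRMS 1, SPMS 2, PPMS 3: mean code = (18 + 14 + 15)/30 = 1.567, covariance = -0.933 × (2 − 1.567) = -0.40.
- Codes RRMS 2, SPMS 1, PPMS 3: mean code = (36 + 7 + 15)/30 = 1.933, covariance = -0.933 × (1 − 1.933) = +0.87.

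The patients are the same and the sign is opposite.

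**Simulation with these inputs and SD 4** (4,000 data sets, two-sided 5% level)

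| Codes (RRMS, SPMS, PPMS) | Mean Spearman | Rejection rate |
|---|---|---|
| 1-2-3 | -0.18 | 15% |
| 3-2-1 | +0.18 | 15% |
| 1-3-2 and 2-3-1 | -0.32 | 42% |
| 2-1-3 and 3-1-2 | +0.32 | 42% |

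One-way ANOVA rejects in 49% and Kruskal-Wallis in about 45%, whatever the labels.

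**One data set of 32 patients** (assumed 18/8/6; observed mean USEQ 24.3, 17.6 and 24.5)

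- Pearson takes the values ±0.19 (p = 0.29), ±0.62 or ±0.66 (both p < 0.001), according to the coding.
- Spearman takes ±0.34 (p = 0.054), ±0.54 (p = 0.001) or ±0.61 (p < 0.001).
- Kruskal-Wallis gives one answer: H = 14.7, p = 0.0006.
- For a six-category profession generated independently of USEQ, Pearson runs from -0.55 to +0.55 and Spearman from -0.48 to +0.48 over all codings.
- For a binary item, the absolute Pearson coefficient stays at 0.476 under every recoding.

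**The case against.** The strongest reply is that the protocol nowhere says that type of MS or profession will be given numbers and correlated with USEQ. That reading joins the analysis sentence to the variable list in another section. The categories' coding is not stated, further detail is deferred to a statistical analysis plan that is not shown, and grouping into two classes would remove the problem. This stands in part: the link is an inference, though a natural one, because the aim, the section heading and the analysis sentence use the same terms. It does not dispose of the point. The article does not simply leave the method open. It names one family of methods for the whole set without any limit, and that family does not fit part of the list.

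The size of the effect is also open to challenge, and rightly. The simulation inputs are assumed, and half of the range from -0.32 to +0.32 is sign reversal from reversing the codes. Under codes 1-2-3, other assumed means favour Spearman: with 26/24/22 its power is about 47% against 40% for ANOVA, and with 26/22/22 about 69% against 63%. With the plan's worst-case SD of 12 and means 26/22/26, every method stays below 10%. A reader might infer that correlation always loses power here; that is not supported. What remains in the two scenarios with other means is that some codings reject no more often than about 5%, and the data give no reason to prefer one coding over another.

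**Conclusion.** The point holds, limited to unordered characteristics with three or more categories: type of MS and profession, plus DMT use and rehabilitation history if recorded that way. For these the stated coefficients depend on arbitrary codes. That dependence is a mathematical fact and needs no assumption about the trial; the figures that illustrate it rest on assumed group sizes, means and SD.

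Two stronger readings are not supported. A reader might infer that aim (iv) as a whole is invalid, but most of its listed characteristics are properly served by the stated method. A reader might also infer that customisation of the programme hangs on these coefficients. The Introduction ties customisation to a better understanding of satisfaction in general, not to aim (iv), and the article presents the study as a pilot for generating hypotheses.

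Severity is minor. The aim is exploratory, and the primary outcome, the sample size and the VRR versus CR comparisons do not change.

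**What to change.** State the method by type of characteristic:

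- **Numeric, ordered or binary** (age, time from diagnosis, EDSS, educational level, sex): keep Pearson or Spearman.
- **Nominal with three or more categories** (type of MS, profession, and DMT use or rehabilitation history if so recorded): report USEQ by category, with differences and 95% confidence intervals from a linear model with indicator variables, or use Kruskal-Wallis.
- **Profession:** group into a few classes fixed before the analysis, since about 30 patients cannot support many categories.

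The cost is one or two sentences in the statistical analysis plan. The procedures are standard in SPSS, which is already planned, and no further data or patients are needed.

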## Abstract

**Background:** Virtual reality (VR) has emerged as a promising treatment approach in rehabilitation for patients with multiple sclerosis (MS) due to its potential to increase patient motivation and rehabilitation adherence. One of the key features for rehabilitation adherence is patient satisfaction with the VR rehabilitation (VRR) program, and information on user satisfaction and not only effectiveness is required to systematically include VRR in routine clinical practice. Given that information on patient satisfaction with VRR is scarce, the primary objective of this study is to assess long-term patient satisfaction with a novel VRR program. This program has been specifically designed for MS patients by a multidisciplinary team of specialists, based on an effective conventional rehabilitation (CR) program. Secondarily, discomfort with VRR will be evaluated, and therapy adherence and changes in a variety of domains typically affected by MS will be compared between patients receiving VRR and patients receiving CR.

**Methods:** In this prospective single-center 6-months follow-up study, 32 and 16 MS patients will receive VRR or CR, respectively. Patients will attend twice weekly rehabilitation sessions on site during 4 weeks, and they will continue with rehabilitation at home for five additional months. Satisfaction, assessed by the User Satisfaction Evaluation Questionnaire (USEQ), at 6 months of the VRR program initiation will be the primary outcome. Secondary outcomes include adherence, disability, spasms and spasticity, balance, fatigue, activities of daily living (ADLs), depression, anxiety, work status, cognition, demographic, and clinical characteristics (in the VRR and CR groups), and discomfort (in the VRR group). Outcome measures will be assessed at baseline, and at 1 and 6 months of rehabilitation initiation.

**Discussion:** The study is intended to provide a better understanding of long-term patient satisfaction with a VRR program specifically designed for MS patients. Additionally, the study will provide information on long-term adherence, changes in motor symptoms, cognitive functions and patient-reported outcomes after the rehabilitation program. The results from this study will help to gather valuable knowledge on the use of rehabilitation with a new VR tool in MS patients.

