### Secondary Outcome Measures

#### Rehabilitation Adherence

Adherence to the on-site rehabilitation sessions will be measured by the number of rehabilitation sessions attended. Participants will be contacted by email or phone if they fail to take part in two consecutive rehabilitation sessions. Rehabilitation adherence at home will be measured by the VR system itself in the VRR group, and by the nurses participating in the study who will require patients in the CR group to indicate via email the frequency with which they have conducted the exercises each week.

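### Unanswered weekly emails in the CR arm count as missing, with no exception for adherence; if patients who stop exercising also stop replying, CR home adherence may be overstated

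*Protocol article*

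**What the plan says.** The Rehabilitation Adherence section of the protocol article sets a different source for the home phase in each arm. For VRR, "Rehabilitation adherence at home will be measured by the VR system itself in the VRR group". For CR, the study nurses "will require patients in the CR group to indicate via email the frequency with which they have conducted the exercises each week".

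The same section provides for follow-up of non-participation: "Participants will be contacted by email or phone if they fail to take part in two consecutive rehabilitation sessions". That sentence comes directly after the text on on-site attendance. Nothing equivalent is stated for an unanswered weekly email.

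The Introduction gives the first secondary aim as to "describe adherence to a VRR and a CR program during 6 months". The Abstract goes further and says that "therapy adherence and changes in a variety of domains typically affected by MS will be compared between patients receiving VRR and patients receiving CR". The Statistical Analysis Plan section keeps to description: "To investigate therapy adherence and discomfort during the VRR program, a descriptive statistical analysis will be performed". It lists mean, SD, median, minimum and maximum, and names no test for adherence.

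The rule on missing data, in the same section, is general: "Absent data will not be accounted for and will be considered missing data. No imputation will be done". It makes no exception for adherence. Further analysis details are deferred to a separate analysis plan.

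**The concern.** For a questionnaire or a walking test, an absent value says little by itself about what the value would have been. Adherence is different. A patient who has stopped exercising has little reason to email a weekly frequency, so silence may be the very behaviour being measured. Under the stated rule that week is missing, not zero.

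The home phase is five of the six months, so most of the adherence measure is exposed. The Discussion itself expects that repetitive conventional exercise may weaken engagement and adherence, and that is the arm in which the rule can hide it.

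Two results are at stake: the single-arm description of CR adherence, and the between-arm reading announced in the Abstract. If weeks without headset use are counted as zero while silent CR weeks are left out, the same behaviour enters one arm's figure and disappears from the other's, to the disadvantage of VRR.

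**Working it through.** The plan states no figure for adherence or non-reply, so there is none of its own to reproduce. What follows is an illustration on assumed values.

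**Inputs from the document.** Home phase of 5 months, about 22 weeks (5 × 52/12 = 21.7). CR arm of 16 patients.

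**Assumptions.** While active, a patient achieves a share *a* = 0.80 of planned home exercise. A share *f* of patients stops after week *t*. A share *s* of the weeks after stopping goes unreported. Active patients always reply.

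**True mean over all W = 22 planned weeks:** a × [(1 − f) + f × t/W]. A VRR log would show the same value if unused weeks count as zero.

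**CR mean over reported weeks with s = 1:** every reported week is an active week, so the mean is *a* = 80% whatever *f* and *t* are. Restricting to patients with complete reports also gives 80%, because only those who never stopped remain.

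| Stoppers | Stop at week 11: true | Overstatement | Stop at week 5: true | Overstatement |
|---|---|---|---|---|
| 12.5% (2 of 16) | 0.80 × (0.875 + 0.0625) = 75% | 5 points | 72.3% | 8 points |
| 25% (4 of 16) | 0.80 × (0.75 + 0.125) = 70% | 10 points | 64.5% | 15 points |
| 50% (8 of 16) | 0.80 × (0.50 + 0.25) = 60% | 20 points | 49.1% | 31 points |

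In relative terms the mid-period overstatement is 80/75 = 1.07, 80/70 = 1.14 and 80/60 = 1.33. These ratios do not depend on *a*.

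**Partial silence** (s = 0.5, 25% stoppers, week 11). A stopper has 11 + 5.5 = 16.5 reported weeks.
- Averaging per patient first: 0.75 × 0.80 + 0.25 × 0.80 × 11/16.5 = 73.3%.
- Pooling weeks: (0.75 × 22 × 0.80 + 0.25 × 11 × 0.80) / (0.75 × 22 + 0.25 × 16.5) = 15.4/20.625 = 74.7%.

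Against a true 70%, the overstatement falls to 3 to 5 points.

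**Cases with no upward bias.** If stoppers reply with zero (s = 0), reported and true means agree. If the variable is the total of reported sessions, a silent week adds nothing, as a zero would, and stoppers' silence does no harm.

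**The opposite case.** If a share *u* of active weeks goes unanswered and each is scored as zero, the CR figure is multiplied by (1 − u) and is too low.

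**The case against.** The strongest reply is that the bias needs several links that the article does not supply.

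- A reader might infer that the home headset records a zero in an unused week. The document does not say so. Logging of exercises and time is described for the on-site HTC Vive interface. The home device is the Oculus Quest, and what it records without use is not stated. A week with no VR record could be absent data under the same rule, and the arms would then be treated alike. This stands. In that case the asymmetry shrinks, but adherence averaged over recorded weeks would be inflated in both arms.
- A reader might infer that silent weeks are dropped from a mean. No denominator is given, and a total count removes the upward bias. This stands, although a total count works only because it treats silence as zero.
- A reader might infer that the silent patients are precisely those who stopped, so that the direction is certain. The nurses actively request reports, stoppers may answer zero, and active patients may forget. Direction and size are therefore both conditional.
- The denominator and the coding of a week without a record are commonly left to the analysis plan, which is not shown. Their absence is no finding. The missing-data rule, however, is stated outright and without exception, and an analysis plan that scored silent weeks as zero would depart from it.
- Scoring every silent CR week as zero could understate CR and favour VRR. This stands, and it is why that version should not be the only headline result.

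**Conclusion.** The point holds conditionally. The document fixes two different sources for home adherence and a blanket rule under which an unanswered CR week is missing. If patients who stop also go silent, and the summary is over reported weeks or over patients with complete reports, CR adherence is overstated. The contrast with VRR is distorted only as far as unused-headset weeks count as zero.

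The size cannot be settled from the document. The 5 to 20 point range rests on assumed stopping shares, stopping at mid-period, complete silence afterwards and 80% adherence while active. Earlier stopping enlarges it and partial replies shrink it.

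The reach is limited. Adherence is a secondary outcome analysed descriptively, and the Abstract's mention of a comparison does not make it a tested one. The primary outcome, the USEQ score in the VRR arm, is unaffected. A change is still worth making, because adherence is the first secondary aim and a few silent patients among 16 move the mean visibly.

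**What to change.** Exempt adherence from the blanket missing-data rule and state the following:

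1. In both arms, the denominator is all planned home weeks to month 6, censored in the same way and only from the date a patient is withdrawn by study rule.
2. In the VRR arm, a week with no VR session counts as zero.
3. In the CR arm, two results are presented side by side: unanswered weeks as zero (lower bound), and replied weeks only (upper bound if silence goes with less exercise).
4. The number of unanswered CR weeks is reported. The record must therefore separate a reply of zero from no reply.

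The cost is a few sentences of analysis wording and a weekly tally of replies; no treatment or visit changes. About half the participants had been enrolled at submission, so the nurses' email records for earlier patients should be checked for item 4. The downside is a range for CR in place of a single figure, whose lower end understates patients who exercised without replying.
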